## Methods

### Study setting

This research builds on existing partnerships between Colorado State University (CSU) and Trees, Water & People (TWP) in Fort Collins, Colorado, USA, and the Honduran Association for Development (Asociación Hondureña para el Desarrollo, AHDESA) in Tegucigalpa, Honduras. The study area included 10 rural communities near the town of La Esperanza in the Department of Intibucá, Honduras. Intibucá is a mountainous region with elevations ranging from approximately 1700 to 2200 m. The study area has an agricultural-based economy, farming potatoes, beans, coffee, and other fruits and vegetables. Households in the region were dependent on biomass fuel (wood) for cooking. Primary and secondary stove types varied from 3-stone fires to modified traditional cookstoves with griddles and chimneys. Most kitchens were enclosed and located in the main house or as a separate building near the main house, and most secondary stoves were located outside.

### Formative research and cookstove selection

In fall 2014, we prepared for the trial by assessing the study population with a convenience sample of over 500 in-person surveys on sociodemographic characteristics, cookstove types, preferences of cookstove models, obstacles to new cookstove adoption, cooking behaviors, and cookstove experts’ perceptions of successes and failures of previous interventions (NIH ES022269). These findings, along with input from our community partners at TWP and AHDESA, supported the selection of the wood-burning *Justa* cookstove for the intervention. The *Justa* cookstove was well-accepted, culturally appropriate, locally sourced, and functioned well when maintained correctly. It was designed specifically for Honduran homes with an insulated rocket-elbow ceramic combustion chamber, chimney, metal griddle, and side soot compartment [30]. The griddle can hold 2 to 3 pots at once, and is also used for making tortillas. Examples of traditional and *Justa* cookstoves are shown in Fig. 1.

**Fig. 1 Fig1:**
[figure not shown]
Examples of a primary traditional cookstove (**a**) and secondary traditional cookstove (**b**), and internal and external views of *Justa* cookstoves (**c**, **d**)

As the next step in our formative research, we conducted a cross-sectional study in spring 2015 among 150 women from the same study population (NIH ES022810). Half of the women were using a *Justa* cookstove received from other projects, and the other half cooked on traditional cookstoves. This study allowed us to test our equipment in the field and refine our data collection procedures. As mentioned above, we observed evidence of associations between exposure to household air pollution and blood pressure [26], prediabetes/diabetes [27], and metabolic syndrome [24], as well as self-reported symptoms among traditional cookstove users compared to *Justa* users [28].

### Trial design

We utilized an individual-level, stepped-wedge randomized controlled trial design, with 230 women using traditional wood-burning cookstoves at baseline. Women were randomly assigned into study arms 1 and 2 by blindly drawing a number from a bag at a community meeting. Six repeated measures occurred over the 3-year study period from August 2015 through May 2018 (Table 1). Study arm 1 (*n* = 115) received the *Justa* cookstove intervention after visit 2, and arm 2 (*n* = 115) received the intervention after visit 4 (Table 1). A unique benefit of the stepped-wedge design is that each study arm provides before and after observations, and each arm switches from ‘control’ status to ‘intervention’ status over the course of the study, but not at the same time [31].

**Table 1 Tab1:** Study scheme for timing and visits of interventions, Honduras, August 2015 – May 2018

Stepped-wedge randomized controlled trial		
Timing of study visits for data collection	Arm 1 (*n*=115) Stove type	Arm 2 (*n*=115) Stove Type
Visit 1: Aug – Dec 2015	Traditional	Traditional
Visit 2: Jan – May 2016	Traditional	Traditional
	Arm 1 receives intervention	
Visit 3: Sep – Dec 2016	*Justa*	Traditional
Visit 4: Feb – May 2017	*Justa*	Traditional
		Arm 2 receives intervention
Visit 5: Sep – Dec 2017	*Justa*	*Justa*
Visit 6: Feb – May 2018	*Justa*	*Justa*

### Recruitment and retention

Communities were selected with guidance from the community advisory board based on traditional cookstove use among households, accessibility from the field house in La Esperanza (within an hour drive), and permission from local leaders to conduct the study within their community. Eligibility to participate included the following criteria: female, 24–59 years of age, primary cook of the household, not pregnant at time of recruitment, non-smoking, not exposed to secondhand smoke, used only a biomass fuel traditional cookstove for cooking. Community meetings were held to introduce the research team and objectives and to obtain a list of people’s names who were interested in enrolling in the study. Women not in attendance at the meeting could still be enrolled if their name was written by a friend or family member, or if they later decided they would like to be screened for eligibility. After the initial study visit, a woman was skipped for data collection if she was pregnant or not home after 2 attempts and revisited for the following study visits.

To motivate women to continue participating for all 6 visits, we offered an incentive of a bag of food items at each visit worth $5 USD. We also offered a one-time secondary incentive of similar perceived value to the intervention cookstove to arm 2 at the time when arm 1 received the *Justa* cookstove, and then to arm 1 at the time when arm 2 received the *Justa* cookstove. The community advisory board helped select secondary incentive options of a radio, kitchen utensils, or a basket of specialty food items, with the criteria that the gift would not influence exposure.

### Implementation and training

Primary materials for the *Justa* intervention cookstoves included a chimney, griddle, combustion chamber and soot compartment, manufactured by AHDESA in Tegucigalpa and donated by the Fondo Centroamericano para el Acceso a la Energía y Reducción de la Pobreza (FOCAEP). Additional materials for stove construction included cement blocks, which were acquired locally in La Esperanza, and households were asked to contribute a table to hold the cookstove (usually a large, immobile, self-constructed adobe base), sifted wood ash, a cardboard box, nails, wooden boards and mud.

Community meetings were held during the first study visit in every village to review the cookstove construction process and discuss the required materials that each family would procure. Participants were required to destroy their traditional cookstove before the new *Justa* cookstove was built, although they could keep their previous base (i.e., table) if it fit the necessary dimensions for the new *Justa* cookstove. A second community meeting was held among study arm 2 participants prior to their *Justa* construction to review the cookstove construction process and discuss the materials. Cookstoves were constructed by AHDESA technicians and the study coordinators.

A few weeks before the first *Justa* cookstoves were constructed, each community received 2 new *Justa* cookstoves for their local elementary schools, donated by the United States Agency for International Development. All participants were invited to observe and ask questions during the construction and testing of the new cookstoves.

Personal training on cookstove use and maintenance occurred for each woman during the *Justa* cookstove construction in her home. The training was identical for all participants, as trainers followed a checklist and review. The training covered the identification of cookstove parts, choice of fuel, fuel size, cleaning, and the maintenance schedule. The women were given a water-resistant poster that provided a summary of the stove maintenance steps and a telephone contact for additional help (Additional file 1: Figure S1). The posters were hung in the kitchens near the new cookstoves. These educational materials and training steps were developed through the guidance of the community advisory board, TWP, and AHDESA. Community leaders for each village served as points of contact for study participants and were informed about the project’s progress at monthly meetings with the research team.

At every study visit following the intervention, the condition and maintenance of the *Justa* cookstove were assessed through women’s self-report and direct researcher observations. The survey questions were identical to the maintenance steps outlined in the educational poster. If certain steps were not being properly followed, the researcher would re-explain the steps and emphasize the reason for the maintenance.

### Study visits

A typical visit involved arriving at the first house for set-up around 7:30 am, greeting the woman, obtaining verbal informed consent by our study coordinator, installing all exposure monitors, and conducting health and kitchen questionnaires. This day 1 set-up usually lasted around 20–25 min. The following day (at least 24 h later), the research team would return to the woman’s house, remove all exposure equipment, complete the health questionnaire and stove maintenance questions, take all health measures, give the woman her incentive, and explain her health results to her (i.e., blood pressure, BMI, HbA1c, cholesterol, and triglycerides). We explained health results to the women using categories of normal/abnormal based on established cut points; however, women were told that the researchers were not medical professionals and could not make diagnoses based on health results, and if she had any worries or questions, she should visit her health center to speak with a healthcare provider (Additional file 2: Figure S2). This day 2 visit usually lasted between 40 and 50 min.

All data collection was completed by 12 noon each day. Study visits took place Monday through Saturday. No samples were collected on Sundays due to the potential to capture atypical cooking behaviors.

### Exposure assessment

Table 2 summarizes all exposure assessments. Our main exposures of interest were assigned cookstove type categories (*Justa* cookstove versus traditional cookstove; Fig. 1), and 24-h gravimetric personal and kitchen household air pollution concentrations (PM_2.5_). Kitchen air pollution monitors were placed within a range of 76–127 cm above the front edge of the cookstove, slightly above the woman’s breathing zone when standing at the stove to avoid interference with her cooking tasks, and away from the direct plume of smoke and windows and doorways (Fig. 2). Kitchen temperature and relative humidity data were measured during each visit and the monitors (Lascar electronics data logger, Erie, PA, USA) were collocated with the kitchen exposure equipment. Personal air pollution monitors were clipped onto a small bag or cloth necklace near the woman’s breathing zone and worn for 24 h, with instructions to only remove the bag/necklace to sleep and bathe and to keep the bag/necklace near the bed while sleeping (Fig. 2). Field blanks were collected once a week. An accelerometer that logged 3-axis movement data was collocated with the personal exposure equipment to estimate compliance of wearing the monitors (X16-1D Accelerometer, Gulf Coast Data Concepts, Waveland, MS, USA).

**Table 2 Tab2:** Summary of health, exposure, and other participant and household measurements

Measurement	Description	Source	Groups Measured	Timing^a^
Primary health endpoints	Blood pressure (brachial systolic and diastolic) C-reactive protein (systemic inflammation) Glycated hemoglobin (HbA1c)	SphygmoCor XCEL monitor Dried blood spots Finger-stick point-of-care instrument	All participants All participants All participants	All 6 visits, day 2 All 6 visits, day 2 All 6 visits, day 2
Secondary health endpoints	Other biomarkers of systemic injury and inflammation Metabolomics Augmentation index and central pulse pressure Blood lipids (LDL, HDL, total cholesterol, triglycerides) Self-reported health symptoms Fractional exhaled nitric oxide (airway inflammation) Telomere length from buccal cells	Dried blood spots Dried blood spots SphygmoCor XCEL Finger-stick point-of-care instrument Questionnaires NIOX Vero and Aero monitors Buccal scrapes	All participants All participants All participants All participants All participants Sub-set of participants Sub-set of participants	All 6 visits, day 2 Visit 1 All 6 visits, day 2 All 6 visits, day 2 All 6 visits, day 2 All 6 visits, day 2 Visits 1-4, day 2
Exposure assessments	Assigned stove type	Randomization	All participants	See Table 1 scheme
	Kitchen			
	PM_2.5_ Black carbon Ultrafine PM Real time and gravimetric PM_2.5_ Carbon monoxide	Triplex cyclone and AirChek pump PM_2.5_ Filters and Sootscan Discmini Personal Data Ram Dräger Pac 7000	All kitchens All kitchens Sub-set of kitchens Sub-set of kitchens All kitchens	All 6 visits, 24-hours All 6 visits, 24-hours Visits 1-4, 24-hours Visits 1-4, 24-hours Visits 1-3, 24-hours
	Personal			
	PM_2.5_ Black carbon Compliance with wearing monitors Carbon monoxide	Triplex cyclone and AirChek pump, UPAS PM_2.5_ Filters and Sootscan Accelerometer Dräger Pac 7000	All participants All participants All participants All participants	All 6 visits, 24-hours All 6 visits, 24-hours All 6 visits, 24-hours Visits 1-3, 24-hours
Other sources of household air pollution	Neighbors, traffic, trash burning, kerosene use Smoking status (cigarettes and puro) Secondhand smoke exposure	Questionnaires Questionnaires Screening	All participants All participants All participants	All 6 visits, day 1 Screening and all 6 visits, day 2 Screening
Stove use	Self-reported use of all cookstoves, behaviors Electronic monitoring of cookstove temperature *Justa* cookstove maintenance, changes, preferences Time cooking separately for animals	Questionnaires Stove Use Monitors (SUMs) Questionnaires Questionnaires	All participants All cookstoves *Justa* recipients All participants	All 6 visits, day 2 All 6 visits, 24-hours Visits 3-6, day 2 All 6 visits, day 2
Household and kitchen characteristics	Elevation and GPS coordinates Kitchen temperature and humidity Kitchen ventilation/openings Kitchen location, size, and housing materials	Maps.me on smart phones EasyLog monitor Questionnaires Questionnaires	All households All kitchens All kitchens All kitchens	Visit 1 (repeated if new house) All 6 visits, 24-hours Visit 1 (repeated if new house) Visit 1 (repeated if new house)
Socioeconomic and demographics	Income sources Material items, electricity, education, beds, age Household size, age of youngest child	Questionnaires Questionnaires Questionnaires	All participants All participants All participants	All 6 visits, day 1 Visit 1, day 1 All 6 visits, day 1
Other health-related measures	Illnesses, previous diagnoses Medication and vitamin use 24-hour dietary recall and diversity Weekly physical activity Body mass index (BMI), waist and hip circumference Pregnancy	Questionnaires Questionnaires Questionnaires Questionnaires Anthropometric measures Screening and Questionnaires	All participants All participants All participants All participants All participants All participants	All 6 visits, day 2 All 6 visits, day 2 All 6 visits, day 2 All 6 visits, day 2 All 6 visits, day 2 Screening and all 6 visits, day 1

^a^Women received six repeated measures over the 3-year study period, with approximately six months between visits. Each study visit included two consecutive days of data collection: day 1 set-up of all exposure monitors, and day 2 take-down of monitors and collection of health measures. Further details on timing and collection procedures can be found in the “Study visits” section

**Fig. 2 Fig2:**
[figure not shown]
Examples of exposure collections: post-sampling filter (**a**), kitchen exposure monitors near cookstove (**b**), and personal UPAS monitor (**c**). Photo credits: [name] (**a**)

Twenty-four hour kitchen and personal PM_2.5_ samples were collected on 37 mm filters (Fiberfilm, Pall Corporation, NY, USA and Teflo filters, VWR, Radnor, PA, USA). PM_2.5_ was sampled by drawing air through a size-selective cyclone inlet (Triplex, BGI, Inc., NJ, USA) using a pump (AirChek XR5000, SKC Inc., PA, USA) calibrated to 1.5 liter (L) per minute (DryCal Lite, Mesa Labs, NJ, USA) prior to each sample. Due to product availability, we switched from Pallflex fiberfilm filters to Teflo filters prior to exposure monitoring for the fifth study visit. Our filter comparison study demonstrated excellent agreement and correlation between paired samples collected in Honduran kitchens (Pearson correlation coefficient, 0.96; *n* = 16 paired observations).

We switched to a different personal exposure monitor starting at the fifth study visit for all participants, called the Ultrasonic Personal Aerosol Sampler (UPAS, Access Sensor Technologies, Fort Collins, CO, USA) (Fig. 2). The UPAS included a miniature piezoelectric pump to draw in air at 1.0 L/minute, with a customized cyclone that captured PM_2.5_ sample on the enclosed filter. It is more compact, lighter (198 g), and less noisy than the original setup [32]. To ensure consistency between the previously used filter sampling system and the UPAS, we conducted a field evaluation in spring 2017 [33]. We observed strong agreement and correlation (Spearman coefficient 0.91) between 43 paired measures [33].

Filters from kitchen and personal PM_2.5_ sampling were stored at − 20 °C prior to transport from Honduras to CSU for post-sampling analysis. At CSU, filters were stored at − 80 °C, equilibrated to weighing-room conditions over at least 24 h prior to analysis, and analyzed gravimetrically to determine PM_2.5_ mass (Mettler Toledo MX5 Microbalance, Mettler Toledo, Columbus, OH, USA). Mass measurements were made in duplicate (or triplicate if the first 2 values differed by more than 5 μg) and averaged. For each sample, PM_2.5_ mass was calculated as the difference between the post- and pre-sampling measurements. The PM_2.5_ limit of detection (LOD) for each phase was estimated by adding the mean mass of the field blanks to 3 times the standard deviation of the field blank masses [34]. Samples that were below the LOD were substituted with the LOD/$$ \sqrt{2} $$. Samples were blank-corrected by subtracting the mean blank mass for the phase. Final 24-h PM_2.5_ concentrations were estimated by dividing the blank-corrected filter mass by the volume of the air sampled through the pump over the measurement period. Pump performance was considered adequate if the calibration flow rate had less than 10% difference between pre- and post-sampling measurements.

Samples were analyzed for black carbon using the same 37 mm Pallfex and Teflo filters as the PM_2.5_ samples. Black carbon concentrations were estimated based on the change in optical transmission of 880 nm light through the filters [35] before and after sampling (Transmissometer model OT-21, Magee Scientific, Berkeley, CA, USA). Pre-sample transmission was measured for study visits 2–6, and estimated for study visit 1. Full methods for black carbon estimation, including measures of attenuation, reference values for transmittance, LOD calculations, and final calculations have been previously described in detail [26].

Time-resolved (1 Hz) particle number concentration (PNC) was measured with a diffusion disc classifier (Discmini, Matter Aerosol, Wohlen, Switzerland), placed in the kitchen for 24-h. Due to having only one PNC instrument, the Discmini was deployed on Mondays, Wednesdays, and Fridays in a subset of 20–40 women during visits 1 to 4. The Discmini was placed within 102 to 178 cm from the front edge of the stove and not directly in front of a window or door. Real-time and gravimetric PM_2.5_ (in addition to the primary PM_2.5_ measurements described above) were measured with the Personal Data Ram (PDR 1200, Thermo Electron Corporation, Franklin, MA, USA) during visits 1–4, and collocated with the Discmini. The PDR was run with a triplex cyclone and AirChek pump, calibrated to 1.5 L/minute, as described above.

Twenty-four hour personal and kitchen carbon monoxide concentrations (parts per million, ppm) were measured in visits 1 to 3 for all participants with the Dräger Pac 7000 (Dräger Safety AG & Co., Lubeck, Germany), which was calibrated prior to each field session with 100 ppm carbon monoxide gas. The resolution for the monitors was 2 ppm [36] and was used as the detection limit. Dräger Pac 7000 instruments were set to log at one-minute intervals. For personal measurements, instruments were collocated on the personal monitor bag worn by the participant; for kitchen concentrations, the Dräger Pac 7000 was collocated with the primary kitchen monitors.

### Health endpoints

Table 2 summarizes all health measurements collected in the study, including primary and secondary health endpoints. All health endpoints were based on non-fasting measures. The 3 primary health endpoints were brachial blood pressure (systolic and diastolic), systemic inflammation via CRP, and HbA1c.

Brachial systolic and diastolic blood pressure were measured as indicators of CVD risk using the SphygmoCor XCEL Central Blood Pressure Measurement System (AtCor Medical Pty Ltd., West Ryde, Australia), which has also been described in our formative research publication [26]. A brachial artery cuff (23–33 cm or 31–40 cm) was placed on the woman’s right arm while she was in a seated position, with her legs uncrossed and feet resting on the floor (Fig. 3). After 10 min of rest, 3 consecutive measurements were recorded. The woman was asked to refrain from speaking or moving during the readings. The average of the 2nd and 3rd measurements were automatically generated by the device for final systolic and diastolic blood pressure estimates. The SphygmoCor XCEL device received regular calibration and maintenance, as directed by the manufacturer.

**Fig. 3 Fig3:**
[figure not shown]
Examples of collection for the primary health endpoints: blood pressure (**a**), dried blood spots C-reactive protein (**b**), and finger-stick sample for glycated hemoglobin (HbA1c) (**c**). Photo credits: [name] (**b**)

To estimate CRP as an indicator of systemic inflammation, dried blood spots were collected via finger-stick from women (Fig. 3). The puncture site on the middle or ring finger on the woman’s non-dominant hand (usually her left hand) was cleaned with 70% isopropanol and allowed to completely dry. A second finger-stick was conducted with the woman’s permission, if the first stick yielded little blood. Following the puncture with the contact-activated safety lancet, the first drop of blood was wiped away with a sterile gauze pad, as this drop may contain an excess of tissue fluids that could cause erroneous results. Up to 5 blood spots were collected onto Whatman protein saver cards, each spot holding 75–80 μl of blood (GE Healthcare Ltd., Forest Farm Industrial Estate, Cardiff, UK). The cards were maintained in a horizontal position during transport back to the field house, dried at room temperature for over 24 h, and stored in a −20 °C freezer in baggies with desiccant and humidity indicator cards in Honduras. Cards were then transported to CSU and stored at −80 °C. Samples will be shipped to the National Health and Environmental Effects Laboratory of the U.S. Environmental Protection Agency (EPA) for analysis, utilizing the V-PLEX Plus Vascular Injury Panel 2 (human) kit for CRP. Women gave consent to store portions of their blood for future measures of possibly important health markers related to smoke exposure.

We measured HbA1c as an indicator of diabetes and metabolic disease risk with the same finger-stick that was used for the blood spots. Approximately 5 μl of blood was used to measure HbA1c, an estimate of average plasma glucose levels for the past 3 months (A1CNow + kit, Bayer Diabetes Care, Sunnyvale, CA, USA) [37].

The secondary health endpoints are briefly described here, with further details in Table 2. Up to 5 dried blood spots were collected as described above for CRP collection, for additional analysis of metabolomics and other biomarkers of systemic injury and inflammation. Central pulse pressure and augmentation index (i.e., an indicator of systemic arterial stiffness) were collected using the same device and procedures as blood pressure (AtCor Medical Pty Ltd., West Ryde, Australia). Waist and hip circumference (measuring tape, cm), weight (scales, kg), height (measuring tape and level against a wall, m) were assessed, and BMI (kg/m^2^) was calculated. Non-fasting blood lipids (mg/dL), including total cholesterol, low-density lipoprotein, high-density lipoprotein, and triglycerides, were measured with the CardioChek kit using 40 μl of blood from a finger-stick (PTS Diagnostics, Indianapolis, IN, USA). To ascertain current respiratory symptoms and symptoms “during cooking activities,” we modified a standardized respiratory symptoms and disease questionnaire developed by the American Thoracic Society [38]. Women self-reported presence or absence of 9 health symptoms at the present moment and also while cooking, including headache, cough, eye irritation, blurry vision, nose irritation, mucous or phlegm, difficulty breathing, wheezing, and throat irritation.

Fractional exhaled nitric oxide (FeNO) was measured to estimate airway inflammation with the NIOX Vero and Aero devices (Circassia Pharmaceuticals Inc., Morrisville, NC, USA). Due to the high costs of the FeNO tests, a subset of 90 women (39%) was randomly selected at the first study visit to conduct the test, and then asked to repeat the test at each subsequent visit. Buccal cells were collected from the same subset of 90 women for visits 1–4 for analysis of telomere length, an indicator of biological aging and potential susceptibility to CVD [39]. Buccal scrapings of left and right sides of the inner cheek were done with 2 child-sized toothbrushes (10–12 scrapes each side, 2 cm head length), preserved in 15 mL of Saccomanno’s buffer, and shipped within 30 days to CSU for storage in a −80 degree Celsius freezer.

Metabolic syndrome, a cluster of cardiometabolic conditions that occur together, will be defined by current international guidelines and modified for non-fasting lipids: waist circumference ≥ 80 cm plus any 2 of the following, triglycerides > 200 mg/dL, high-density lipoprotein < 50 mg/dL, systolic blood pressure ≥ 130 mmHg, diastolic blood pressure ≥ 85 mmHg, and HbA1c > 5.6% [24, 40, 41].

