For the exposure-response analysis, we will use a linear mixed model similar to the model used in the intent-to-treat analysis. In this framework, the personal and kitchen PM_2.5_ measurements will be included as the exposure variable *x*_*ij*_ in Eq. (1). As the exposure-response approach will not utilize the study’s randomization to control for confounding, potential confounders identified a priori will be included in Eq. (1) as additional fixed effect terms. Potential confounders include participant age, indicators of socioeconomic status (e.g., household possessions, participant education level, beds per person in each household), physical activity levels, BMI, and dietary intake. We will also conduct a “per protocol” analysis using self-reported actual cookstove use, rather than assigned cookstove.

We will evaluate effect modification by adding the following variables as interaction terms with the stove assignment or exposure measurement variable in separate models: age (< 40 or ≥ 40 years), blood pressure (normal systolic < 120 and diastolic < 80 vs. borderline high/high systolic ≥ 120 or diastolic ≥ 80), diabetes status (normal hbA1c < 5.7% vs. pre-diabetic/diabetic ≥ 5.7%), BMI (normal < 25 or overweight/obese ≥ 25), waist circumference (< 80 cm vs. ≥80 cm), and metabolic syndrome (presence vs. absence).

Sensitivity analyses will be conducted to assess the impact of different forms of the adjustment for time in Eq. (1) by varying the number of spline functions and considering alternative representations such as indicators of season or visit number. We will also conduct sensitivity analyses that exclude women who were taking medications that could influence inflammation in the body, such as hypertension or vitamins, or who were ill at the time of the health measurements. Additional sensitivity analyses will exclude air pollution samples that came from pumps that ran for less than 24 h, and flow rates that strayed outside the 10% pre- and post-sampling range.

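### As written, the metabolic syndrome rule counts systolic and diastolic pressure as two items, so blood pressure can supply both of the two required items (minor)

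*Protocol article*

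**What the plan says.** The Health endpoints section of the protocol article introduces metabolic syndrome as "a cluster of cardiometabolic conditions that occur together". It says the syndrome "will be defined by current international guidelines and modified for non-fasting lipids", and then gives the rule: a waist of at least 80 cm "plus any 2 of the following". The list that follows has two lipid items, "triglycerides > 200 mg/dL, high-density lipoprotein < 50 mg/dL", and then "systolic blood pressure ≥ 130 mmHg, diastolic blood pressure ≥ 85 mmHg, and HbA1c > 5.6" percent. That makes five comma-separated items, and nothing joins the systolic and diastolic limits into one.

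The Statistical analysis section uses the result as a binary modifier, "metabolic syndrome (presence vs. absence", one of six modifiers each entered as an interaction in its own model. Aims 1 and 2 both name it. In the same list of modifiers, the raised blood pressure category is defined as systolic of at least 120 or diastolic of at least 80, so there the two pressures form a single condition.

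**The concern.** The rule is stated completely enough to be programmed, and someone coding it as printed would count to two out of five. Systolic and diastolic pressure are two readings of one condition. A woman who exceeds both limits has therefore already met the count, with no lipid or HbA1c abnormality. That sits badly with describing the syndrome as a cluster of conditions. It is not covered by the one modification the text declares, and it differs from how the article combines the two pressures for its own blood pressure modifier.

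At stake is who falls on the positive side of a prespecified effect modifier. Anyone added by the literal reading has waist of at least 80 cm, systolic of at least 130 and diastolic of at least 85. She is therefore already in the large-waist stratum and the raised-pressure stratum of two other modifiers. Her inclusion makes the metabolic syndrome contrast resemble those two more closely and adds no lipid or glycaemic information.

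**Working it through.** No sample size, power or other figure in the article depends on this definition, so there is no stated number to reproduce. The check has two parts.

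**1. Logic of the rule, from the text alone.** Fix waist at 80 cm or more. Each of the five items (triglycerides T, HDL H, systolic S, diastolic D, HbA1c A) is either met or not, which gives 2^5 = 32 patterns.

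- *Literal rule*, T + H + S + D + A ≥ 2. It fails for the one pattern with no item and the five patterns with one item, so it is met by 32 − 1 − 5 = 26 patterns.
- *Joined rule*, T + H + (S or D) + A ≥ 2. If none of T, H, A is met, it fails for all 4 pressure patterns. If exactly one of T, H, A is met (3 ways), it fails only when both pressures are normal, which is 3 patterns. It is met by 32 − 4 − 3 = 25 patterns.
- The rules differ in one pattern: S and D both met, and T, H and A all not met. There the literal rule says present and the joined rule says absent.

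The literal rule can therefore only add positives. Raised systolic alone or raised diastolic alone counts once under either rule.

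**2. Illustration of size.** The share of all women reclassified is

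P(waist ≥ 80) × P(S and D both high) × (1 − p_T)(1 − p_H)(1 − p_A),

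if waist, pressure, lipids and HbA1c are taken as independent.

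From the article: systolic SD 12 mmHg (sample size paragraph) and n = 230. Everything else is assumed: mean pressure 115/70 to 125/80, diastolic SD 9, systolic–diastolic correlation 0.6 to 0.8, bivariate normality, waist ≥ 80 cm in 70%, high triglycerides in 10–30%, low HDL in 30–80%, raised HbA1c in 15–40%.

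| Setting | Both pressures high | No other item | Reclassified | Of 230 |
|---|---|---|---|---|
| Lowest: 115/70, r 0.6; 30/80/40% | 0.024 | 0.7 × 0.2 × 0.6 = 0.084 | 0.7 × 0.024 × 0.084 = 0.0014 | 0.3 |
| Middle: 120/75, r 0.6; 20/50/30% | 0.075 | 0.8 × 0.5 × 0.7 = 0.280 | 0.7 × 0.075 × 0.280 = 0.0147 | 3.4 |
| Middle: 120/75, r 0.8; 20/50/30% | 0.099 | 0.280 | 0.7 × 0.099 × 0.280 = 0.0194 | 4.5 |
| Highest: 125/80, r 0.8; 10/30/15% | 0.221 | 0.9 × 0.7 × 0.85 = 0.5355 | 0.7 × 0.221 × 0.5355 = 0.083 | 19.1 |

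The percentages in the first column are for triglycerides, HDL and HbA1c. At the middle setting the joined rule classes 0.261 (r 0.6) or 0.253 (r 0.8) of women as positive, so the literal rule adds 1.5 to 1.9 percentage points to about 25–26%.

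**The case against.** The strongest reply is that the list may be shorthand. The definition is said to follow international guidelines, which are not at hand. If those treat blood pressure as one criterion and the derivation follows them, every woman is classed as intended and only the sentence is loose. If they do not, the article may simply follow its source. This stands. A reader might infer that women are being misclassified, but that needs a reference definition the article does not show. What the text does establish is that the printed rule allows double counting and is inconsistent with the article's other treatment of blood pressure.

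A reader might also infer that women with a single abnormality are labelled as having the syndrome. That is not so: the waist criterion is mandatory, so the woman in question has a large waist and raised pressure. The cluster description gives no minimum number, so the tension with it is real but falls short of a contradiction.

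Nor does high blood pressure in general satisfy the count; both limits must be exceeded. The share of women over both limits (0.024 to 0.221 under the assumptions above) is not the measure of impact either. It has to be reduced to those with a large waist and no other abnormal item.

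Finally, any definition of the syndrome that includes blood pressure, waist and HbA1c will overlap with the separate modifiers on those measures. Joining the two pressures removes only the extra overlap from the one disputed pattern. The modifiers are fitted in separate models, so the overlap harms no model's fit. This also stands and limits the weight of the point.

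**Conclusion.** The point holds as a minor one. The printed rule lets blood pressure fill both of the two required places. That feature is undeclared and does not match the single blood pressure condition in the Statistical analysis section. The logical result, one pattern in 32 and always towards more positives, rests on the text alone. The number of women does not. About 0.1% to 8% (0.3 to 19 of 230), with roughly 3 to 5 at a middle setting, depends on assumed means, diastolic SD, correlation, prevalences and independence, with only the systolic SD and the sample size taken from the article.

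The consequence is confined to the metabolic syndrome interaction analyses under Aims 1 and 2. Metabolic syndrome is not listed as a primary or secondary endpoint, and the primary model and the power calculation do not use it.

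**What to change.** State whether systolic and diastolic pressure are one criterion or two, and reconcile the definition in the Health endpoints section with its cited guideline and with the blood pressure modifier in the Statistical analysis section. Unless double counting is intended, rewrite the list as four items: triglycerides above 200 mg/dL; HDL below 50 mg/dL; systolic at least 130 or diastolic at least 85 mmHg as one item; HbA1c above 5.6%. Keep waist of at least 80 cm plus any two, and derive the modifier that way. If double counting is intended, declare it as a second modification of the guideline alongside the one for non-fasting lipids.

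The cost is one line of text and one line of derivation code, with no new data. A count of the women in the single disputed pattern would replace the assumed range above with the actual number.
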